#### Recruitment

Participants are recruited from the general New Zealand population, using advertising in newspapers, magazines, on social media, radio, websites, flyers and posters, existing networks and word of mouth. In total, we aim to randomise 1000 participants. We will include as many Māori (indigenous New Zealanders) as possible. We are engaging with Māori networks to develop Māori-targeted recruitment videos and will continue to engage with these networks where appropriate.

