#### Experimental procedures

A flow diagram of the experimental phase is provided in Fig. 2. Participants complete the entire study online, using our Price ExaM website (https://diet.auckland.ac.nz/content/priceexam-join). The website contains all forms (registration, consent, questionnaires), the VS software for download, and instruction material (including manuals and videos) (Fig. 3). Following registration and consent, participants are able to download the VS onto their computer. Next, they will login with their email address. At their first login, participants will be asked to complete a tutorial where they must find and purchase six products in the VS. This tutorial helps participants to become familiar with the software. After completing the tutorial, participants are asked to set their shopping budget. This budget is the approximate total amount they can spend during each shopping task and the amount must cover food purchases and beverages (including alcohol) only (i.e., the VS does not contain non-food products such as soap or toothpaste normally found in a supermarket). Previous studies revealed that participants find it difficult to estimate their weekly supermarket food purchasing budget, therefore we provide them with a range of examples. Participants must spend at least 50 % of their allocated budget and may overspend to a maximum of 125 % to warrant a realistic shop. On each of the five shopping occasions, participants will be instructed to buy the groceries for their household for the coming week just as they would in real life. They will be asked to complete their shops roughly one week apart from each other. We assume a five-week period is long enough to capture staple purchases that people might not buy every week. Participants will receive regular automated text and email reminders during the study to remind them about completing the virtual shops and questionnaires.

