#### Randomisation

For each of the five shops, participants will be randomly allocated to one of the 5000 price sets, without replacement, using a random number generator. Therefore, participants do not receive price sets within the same policy option for each shop and randomisation is not stratified (i.e., it is completely random).

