#### Outcome measures

The main output of the VS experiment will be the multiple observations of price configurations and purchased amounts which can then be used to calculate three main outcomes:A.**Differences in food purchases between the broad food pricing policy options** (Table 1). The following food purchasing measures will be compared between the broad food pricing options that participants have been randomised to:Mean quantity (adjusted for household size) of key nutrients, including saturated fat (g/100 g and % energy), total sugar (g/100 g and % energy), sodium (mg/100 g) and energy content (total KJ and KJ/100 g) of the total shopping basket.Nutrient profiling score of the total shopping basket calculated using the Food Standards Australia New Zealand (FSANZ) nutrient profiling standard [34].Mean quantity (g/ml) (adjusted for household size) of food groups most impacted by the five fiscal food policies (e.g., SSB’s, snacks, fruit and vegetables, etc.).

Statistical analyses will be performed by the study statistician at the end of the experiment, using SAS version 9.4 (SAS Institute Inc., Cary, NC, USA). All randomised shops for all participants will be included in the analysis, on an intention-to-treat basis. Random effects mixed model will be used to test the differences in effect of policy options on food purchase outcomes, adjusting for important socio-demographic variables (sex, age, and ethnicity). Correlation between repeated shopping data collected from the same participant will be taken into account using a random subject effect.B.**Food price elasticities** estimated using the VS output and traditional econometric and/or Bayesian modelling methods (see Step 3 below).C.**Health gains/losses and net healthy system costs** for each tax/subsidy policy calculated through the BODE^3^ (Burden of Disease Epidemiology, Equity & Cost-Effectiveness Programme) MSLT “DIET” model (under development; similar to the BODE^3^ Tobacco model [35]). This model estimates QALYs and net health system cost impacts arising due to changing diets that then lead to changing disease incidence rates and then to changing mortality and morbidity rates (see Step 4 below).

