For each of the three main outcomes, we will examine (pre-specified) interactions by important population groups, including by ethnicity (Māori versus non-Māori), sex and age, noting the limited power. Furthermore, we will measure price sensitivity; shoppers tend to be heterogeneous with regard to their attention and reaction to price and price promotions, which we will account for in our models. Lichtenstein et al., developed and validated a questionnaire to measure price sensitivity [36] from which we will include questions on the factors ‘value consciousness’, ‘price consciousness’ and ‘price mavenism’ (mavenism is how attuned one is to market and price conditions). Price sensitivity questions will be asked right before the first shop (both to measure price sensitivity and to prompt participants to focus on food prices in the VS) and after the first and last shop (where questions will be worded to reflect price experiences during the virtual shopping task).

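### The outcome A mixed model names no term for shop number, although a shop-order effect is plausible; adding one is a nearly free gain in precision

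*Protocol article*

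**What the plan says.** All references are to Step 2 of the Protocol article.

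- **Model (Outcome measures, outcome A).** Policy options are compared in a random effects mixed model "adjusting for important socio-demographic variables (sex, age, and ethnicity". Correlation between one person's shops "will be taken into account using a random subject effect". No term for shop, week or period is named here or elsewhere in the article.
- **Analysis set (same section).** "All randomised shops for all participants will be included in the analysis, on an intention-to-treat basis".
- **Size and structure.** Recruitment: "In total, we aim to randomise 1000 participants". Experimental procedures: each person does five shops, and "They will be asked to complete their shops roughly one week apart from each other".
- **Allocation (Randomisation).** A price set is drawn for each shop, and "randomisation is not stratified (i.e., it is completely random".
- **Price questions (Outcome measures).** A questionnaire is given right before the first shop, "both to measure price sensitivity and to prompt participants to focus on food prices in the VS". Price questions are asked again after the first and the last shop.
- **New software (Experimental procedures).** Participants first find and buy six products in a tutorial: "This tutorial helps participants to become familiar with the software".

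**The concern.** With five shops per person and a new random price set at each, policy contrasts draw heavily on comparisons within a person. Once a subject effect is fitted, sex, age and ethnicity explain almost none of the variation between one person's shops. Shop number does vary within a person, and it follows directly from the five-shop structure.

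The article gives two reasons why shop 1 might differ from shops 2 to 5. The main one is the deliberate prompt to attend to prices, placed right before shop 1 in a study of how people respond to prices. The other is unfamiliar software, which the tutorial reduces but may not remove. If the average basket does shift between shops, a model without a shop term puts that shift into the residual of every policy contrast. What is at stake is some precision, in a study that lists precise estimation among its aims and notes limited power for its interactions by ethnicity, sex and age.

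**Working it through.** **No figure to reproduce.** The article gives no alpha, power, SD, effect size or order-effect size. The design count agrees with itself: 1000 participants × 5 shops = 5000 shops = 5000 price sets.

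**Inputs.** Five shops per person and completely random allocation at each shop come from the article. The size of the shop-1 shift, d, in units of the within-person residual SD, is an assumption.

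**Formula.** A shift d confined to one of five shops has variance 0.2 × 0.8 × d² = 0.16 d² over all shops. Because policy is independent of shop number, this adds to the residual variance, so the ratio of standard errors (without / with shop number) is √(1 + 0.16 d²).

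This is the lower end. If the contrast is estimated wholly within persons, the shift contributes a sum of squares of 5 × 0.16 d² = 0.8 d² per person on 4 within-person degrees of freedom, so the excess is 0.8 d² / 4 = 0.20 d². A random-intercept model lies between the two.

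**Power.** For a contrast with 80 % power when shop number is in the model (two-sided 5 %), power without it is Φ(2.802 / ratio − 1.960). The lower-end ratio is used here.

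| Assumed d | 0.16 d² | Excess SE, lower end | 0.20 d² | Excess SE, wholly within person | Power without the term |
|---|---|---|---|---|---|
| 0.3 | 0.0144 | 0.7 % | 0.018 | 0.9 % | 79.4 % |
| 0.5 | 0.0400 | 2.0 % | 0.050 | 2.5 % | 78.4 % |
| 0.8 | 0.1024 | 5.0 % | 0.128 | 6.2 % | 76.1 % |

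A steady drift over the five shops gives similar values: a total drift of 0.5 SD has variance 0.125 × 0.25 = 0.031, an excess of about 1.6 % in standard error.

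**Simulation check.** There were 400 runs per setting, with 1000 people × 5 shops, equal subject and residual SD, and random allocation in the proportions of Appendix 2. The contrast was saturated fat tax (250 + 250 = 500 shops) against no policy (750 shops), with a true effect of zero.

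| d | Model SE without shop | Model SE with shop | Ratio |
|---|---|---|---|
| 0.2 | 0.0635 | 0.0633 | 1.003 |
| 0.5 | 0.0647 | 0.0633 | 1.022 |
| 1.0 | 0.0690 | 0.0633 | 1.090 |

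At d = 1.0 the two formulas give √1.16 = 1.077 and √1.20 = 1.095, and the simulated 1.090 lies between them. Over all settings, including d = 0, the mean estimate without shop number stayed between −0.003 and +0.004, and coverage of nominal 95 % intervals was 0.948 to 0.963. The omission therefore produced no bias and no undercoverage.

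**The case against.** The strongest reply is that a journal article leaves model detail to the full protocol and the SAP, which are not shown. The sentence quoted describes the socio-demographic adjustment and does not claim to list every term. This is fair, and the SAP may already contain a shop term. But the article does fix a model type, a covariate list and a way of handling repeated shops, and an improvement to that stated model can be suggested.

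A reader might also infer more than the article supports:

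- **That the model adjusts for fixed personal traits alone.** It does not. Outcome quantities are adjusted for household size, and price sensitivity is to be accounted for in the models. These are described as differences between households or shoppers, however, and do not stand in for shop order.
- **That the design produces an established order effect.** No section states that one exists, or its size. Some features work against it: the tutorial comes before shop 1, participants are told that prices vary, price questions are repeated after shop 1, and spending is held to 50–125 % of budget at every shop.
- **That the policy estimates are biased or their standard errors wrong.** Complete randomisation at each shop rules this out, and the simulation agrees.
- **That a shop main effect would reveal a fading price prompt.** A prompt to look at prices would act mainly on the response to price, which is a policy-by-shop interaction. This objection stands, and it is why a separate check is needed.
- **That the demand system in Step 3 should get the same term at no cost.** If the 22 to 24 categories of the prior matrices carry over (an assumption), four shop terms in each free equation add 4 × 21 = 84 to 4 × 23 = 92 parameters, and the elasticity matrices offer no prior for them. Eq. 1 is also given only as an example form. No change to it is proposed.

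The covariates themselves are not at fault. Sex, age and ethnicity are needed for the planned interactions.

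**Conclusion.** The point holds as a minor one, limited to outcome A. The stated model has no shop-number term, its named covariates are constant within a person, and the price prompt right before shop 1 makes an order effect plausible. The loss is in precision alone. At 0.5 SD a contrast with 80 % power would fall to about 78 %, and at 0.2 SD the effect is negligible. These figures rest on an assumed shop-1 shift, on a shift common to all participants, and on five completed shops per person. If there is no order effect, the term gains nothing and costs almost nothing.

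**What to change.** 1. In the outcome A mixed model, add shop number (1 to 5, categorical) as a fixed effect alongside policy option, sex, age, ethnicity and the random subject effect. The cost is 4 degrees of freedom per model, out of up to 5000 shops. Design, data collection and randomisation do not change.
2. As a sensitivity analysis, report the policy effects with shop 1 excluded, or fit a policy-by-shop-1 interaction. Either addresses whether the response to price depends on the prompted shop, which the main effect cannot do. Excluding shop 1 drops a fifth of the data, so standard errors grow by about √(5/4) = 1.12 (pooled over shops) to √(4/3) = 1.15 (wholly within person). The main analysis should therefore keep all randomised shops, as the article plans. The interaction keeps all the data but needs extra parameters.

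If the SAP already contains a shop or period term, item 1 is met and only item 2 needs checking.

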#### Ethics approval

The experimental phase began in February 2016 and will continue for 10–12 months until recruitment targets are reached. Ethical approval was obtained from the University of Auckland Human Participants ethics committee on 10/11/2015 (reference 016151) for three years.

### Step 3: estimation of price elasticities

#### Overview

Following the VS experiment, in Step 3, we will use the output data (i.e. multiple observations of price configurations and purchased amounts) as inputs to econometric models to estimate more accurate and precise PEs. We base our analysis on the Bayesian estimation approach to exploit results from the previous literature. This method also provides us with a powerful tool to address censoring in the data. Estimation of the demand system via the Bayesian approach requires prior assumptions about the model parameters as an input into the estimation process. As the PEs are a function of the parameters in the demand models, this enables us to incorporate PEs from the literature (The New Zealand SPEND study [29]) as part of the prior assumptions for the model parameters using the functional relationship between PEs and model parameters and additional constraints on the range.

The prior information, summarised in terms of the prior distributions of the parameters, is combined with the information from the data, summarised in the likelihood, to obtain the posterior distributions of the model parameters as well as the PEs. Point estimates and standard deviations of the model parameters and PEs are then computed from these posterior distributions.

#### AIDS model

The empirical analysis to obtain PE estimates from the data is based on an AIDS model [37], for example of the following form:1$$ {\mathrm{w}}_{\mathrm{i}}={\upalpha}_{\mathrm{i}}+{\displaystyle \sum_{\mathrm{j}=1}^{\mathrm{n}}}{\upgamma}_{\mathrm{i}\mathrm{j}} \ln {\mathrm{p}}_{\mathrm{j}}+{\upbeta}_{\mathrm{i}} \ln \left(\frac{\mathrm{X}}{\mathrm{P}}\right)+{\upvarepsilon}_{\mathrm{i}} $$

where: w_i_ is budget share of good i, i = 1,..,n; p_j_ price of food j; X is total food expenditure; P is price index; α_i_, γ_ij_ and β_i_ are parameters to estimate; and ε_i_is the error term.

Price elasticities (PE) are calculated as follows [38, 39].2$$ {\in}_{\mathrm{i}\mathrm{j}}=\frac{\upgamma_{\mathrm{i}\mathrm{j}}-{\upbeta}_{\mathrm{i}}{w}_j}{w_{\mathrm{i}}}-{\updelta}_{\mathrm{i}\mathrm{j}} $$

where: $$ {\updelta}_{\mathrm{ij}}\left\{\ \begin{array}{c}\hfill =1,\kern0.75em \mathrm{i}=\mathrm{j}\hfill \\ {}\hfill =0,\kern0.75em \mathrm{i}\ne \mathrm{j}\hfill \end{array}\right. $$

Income elasticity is given by3$$ {\upeta}_{\mathrm{i}}=\frac{\upbeta_{\mathrm{i}}}{{\mathrm{w}}_{\mathrm{i}}}+1 $$

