#### Bayesian methods

The estimation of the demand model requires an assumption of prior distributions of the model parameters. As is standard in the literature, normal distributions will be assumed for the model parameters, chosen partially due to their computational aspects. Prior means for the model parameters informing the PEs, {β_*i*_} and {γ_ij_}, will be specified with the help of two matrices of PE estimates from BODE^3^ [40] and SPEND [29], ∈ _ij_^BODE3^ and ∈ _ij_^SPEND^, respectively. The PE matrix from BODE^3^ consisted of 22 food categories with PE values adapted from the literature for developed countries. The PE matrix from SPEND was estimated from the Household Economic Survey data in New Zealand for 24 food categories.

Equation (2) will be used in connection with the PE matrices to construct priors for demand equation parameters: α_i_, γ_ij_ and β_i_ in Eq. (1). Since the number of parameters to calculate is larger than the number of prior PEs, we will also use a prior simulation approach in connection with additional assumptions to set reasonable prior means for all parameters.

We will then develop an algorithm that accommodates these priors and zero expenditures to estimate a demand system using an AIDS model as detailed from Eqs. (1, 2 and 3).

Steps to estimate the Bayesian AIDS model include:Specify functional form for the demand model, which is an AIDS equation system.Convert prior PE matrices to prior mean parameters in the demand model.Use Monte Carlo simulation to draw values for the prior parameters from specified distributions.Use Bayesian approach to combine the prior information for the parameters with the data from the VS experiment to obtain estimates for these parameters based on their posterior distributions.Calculate PE values from the posterior distributions of parameters.

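### Eq. (1) uses total household food spend without household size, so beta_i partly reflects family size and chance basket size, and Eq. (3) is a food-expenditure elasticity, not an income elasticity (minor)

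*Protocol article*

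**What the plan says.** The Step 3 section headed AIDS model gives Eq. (1). The outcome w_i "is budget share of good i", and the regressors are the log prices and ln(X/P), where "X is total food expenditure; P is price index". Household size does not appear. Eq. (3), beta_i/w_i + 1, is introduced with the words "Income elasticity is given by".

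The form is offered as an illustration: the analysis "is based on an AIDS model [37], for example of the following form". The section on Bayesian methods then commits to it, saying the algorithm will "estimate a demand system using an AIDS model as detailed from Eqs. (1, 2 and 3".

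The data come from Step 2. Under Experimental procedures, "participants will be instructed to buy the groceries for their household for the coming week". Before the first shop, "participants are asked to set their shopping budget", and the spend in each shop must lie between 50 % and 125 % of that amount. Price sets are randomised shop by shop. In Outcome measures, part A, quantities are "adjusted for household size", so household size must be collected. Price elasticity estimation promises compensated and uncompensated, and conditional and unconditional, PEs.

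**The concern.** Randomisation protects the price coefficients. It does not protect beta_i, because X is chosen by the participant. Two things other than affluence enter beta_i:

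- **Family size.** Larger households spend more in total. If their shares also differ, beta_i absorbs that difference.
- **Chance basket size.** If X is the total of the same basket that forms w_i, an unusually large purchase of group i raises both w_i and X, which pushes beta_i up. A chance change in the rest of the basket moves X and w_i in opposite directions, which pushes beta_i down. More shops do not remove either effect.

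At stake are the expenditure elasticities and the quantities built on them, namely compensated and unconditional PEs. Calling Eq. (3) an income elasticity adds to the problem, because X is spend on food and not income.

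**Working it through.** The protocol gives no elasticity or precision figure on this point, so there is nothing to reproduce.

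**1. What identifies beta_i.** Spend may run from 0.50 to 1.25 of budget. One household's X can therefore vary by 1.25/0.50 = 2.5-fold, or ln 2.5 = 0.92 log units, with affluence unchanged. Randomised prices help little. In Appendix 1, Ratio1 is uniform on 0.85 to 1.15, with SD 0.30/√12 = 0.087. Averaged over 21 categories (equal weights assumed), its part of the price index has SD 0.087/√21 = 0.019 before taxes. Beta_i therefore rests mainly on self-chosen X.

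**2. Where an error goes.** Let beta_i be wrong by b.
- Eq. (3): the expenditure elasticity is wrong by b/w_i.
- Eq. (2), gamma held fixed: the own-PE shifts by −b and a cross-PE by −b·w_j/w_i.
- Gamma is not held fixed, however. With ln P ≈ Σ w_j ln p_j, the fitted coefficient on ln p_j is gamma_ij − beta_i·w_j, the numerator of Eq. (2). Randomised prices estimate that combination well whatever beta_i is, provided ln X is only weakly related to the prices. An error in beta_i is thus largely offset by gamma_ij.
- Compensated PE = uncompensated PE + w_j × expenditure elasticity, so it shifts by w_j × (elasticity error). At an assumed w_j of 0.15 and an error of 0.39, that is 0.15 × 0.39 = 0.06.

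**3. Single-group simulation (all inputs assumed).** 1000 households × 5 shops; true expenditure elasticity 1.00 and own-PE −1.00; mean share 0.02, 0.05 or 0.15; budget rising with household size (exponent 0.5) and affluence (log SD 0.4); share changing by 0 or ±0.2w per unit ln(household size); chance log SD of spend on the group 0.3 or 1.0 and on the rest 0.15; prices U(0.85, 1.15) × U(0.85, 1.15); only shops at 50–125 % of budget kept; least squares, 40 replicates. Selected mean expenditure elasticities:

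| Share | Size effect on share | Chance SD | Eq. (1) as written | + ln size | + ln size, budget as instrument |
|---|---|---|---|---|---|
| 0.05 | 0 | 0.3 | 0.95 | 0.93 | 1.00 |
| 0.05 | −0.01 | 0.3 | 0.84 | 0.93 | 1.00 |
| 0.05 | +0.01 | 0.3 | 1.06 | 0.93 | 1.00 |
| 0.05 | 0 | 1.0 | 1.08 | 1.11 | 1.00 |
| 0.02 | −0.004 | 0.3 | 0.82 | 0.91 | 1.00 |
| 0.15 | +0.03 | 1.0 | 1.26 | 1.24 | 1.00 |

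Over all 18 scenarios the ranges were 0.82–1.26, 0.91–1.24 and 0.99–1.00. Household size alone moved the elasticity by about ±0.1; chance basket size alone gave 0.94 to 1.17. The own-PE stayed between −1.04 and −0.98 as written and between −1.05 and −0.98 after correction. The largest gap within a scenario was −1.042 against −1.011, or 0.03. This check did not deflate X by P, so the offset in step 2 was switched off.

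**4. Multi-group simulations (also assumed inputs, least squares).**
- Twelve groups, 1000 × 5 shops, shares driven by per-person spend, lognormal basket shocks with SD 0.5–0.8: elasticity errors −0.25 to +0.24 as written; −0.25 to +0.09 with ln size; at most 0.05 with ln size and the budget instrument. In a run on the same lines, the largest mean difference in an uncompensated cross-PE between the as-written and instrumented fits was about 0.01, against a sampling SD of 0.06–0.10. Compensated PEs differed by a median of 0.007–0.008 and at most 0.07.
- A further set of assumed inputs: errors about −0.20 to +0.39 as written; within 0.07 with ln size; within 0.03 with both. Uncompensated own- and cross-PEs moved by 0.02 or less, compensated PEs by at most about 0.06.

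**The case against.** The strongest reply is that Eq. (1) is an example in a journal article. Other parts of the protocol promise features that it does not show: PEs by income level and ethnicity, interactions by sex and age, heterogeneity in price sensitivity, and handling of zero expenditure. A household-size term or a treatment of endogenous expenditure could sit in the full plan in the same way. This stands in part. A reader might infer that household size is excluded from estimation, and the document does not establish that. What it does establish is the model as displayed, the commitment to estimate from Eqs. (1) to (3), and the income label on Eq. (3).

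Three further replies also stand. The protocol does not say that X is the total of the same shop; that is inferred from w_i being a share of X and from shop-level price randomisation. If X were a total over several shops, the family-size part would remain. The simulations use least squares, whereas the plan is Bayesian with informative priors and censoring, which would change beta_i by an unknown amount. And the instrument works in the simulations because it was made valid there. The real budget is also self-chosen, and the protocol itself notes that people find theirs hard to estimate.

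A reader might also infer that the study's price elasticities, and hence its health modelling, are undermined. The documents do not support that: prices are randomised, the uncompensated PEs hardly move, and expenditure elasticity is not one of the three main outcomes. Nor should one argue from participant-level fixed effects, since Step 3 proposes none.

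**Conclusion.** The point holds as a minor one. As stated, Eq. (1) lets beta_i carry family size and chance basket size, and Eq. (3) is an elasticity with respect to total food spend, conditional on that spend, not an income elasticity. Under assumed inputs the expenditure elasticities are wrong by an order of 0.1 to 0.4, in either direction. The knock-on to compensated PEs is small, about 0.06 at most (0.07 in one variant). Unconditional PEs also use beta_i, but the effect on them was not quantified. Uncompensated own- and cross-PEs are close to unaffected. The mechanism follows from the equations and the shopping rules. The sizes depend on the assumed link between household size and shares, the assumed chance variation in baskets, and least-squares estimation; they show order of magnitude and are not estimates for this study.

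**What to change.** 1. Add ln(household size) to Eq. (1). Alternatively use per-person X, which is more restrictive because it fixes the household-size coefficient at −beta_i.
2. State whether X is the observed spend of the same shop.
3. Relabel Eq. (3) as a conditional food-expenditure elasticity.
4. At least as a sensitivity analysis, treat ln X as endogenous: regress it on the log of the budget set before the first shop and the other regressors, and include the residual in Eq. (1) as a control-function term. State the assumption this needs, that the budget does not itself reflect tastes for particular food groups.
5. Use the same beta_i in Eq. (3) and in the compensated and unconditional PEs.

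The cost is one covariate and one extra term, from data already collected, and slightly wider intervals for the expenditure elasticities. Household size alone may not be enough: in the simulations the remaining error ranged from within 0.07 to about 0.25, depending on the assumed basket variation. That is the reason for item 4.
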